### Primary outcomes measures

Patient length of stay will be measured as the number of overnight stays in the rehabilitation unit, from the day of admission until the day of discharge from the unit. Length of stay is the largest contributor of direct care costs during rehabilitation [32,33].

The EuroQol questionnaire (EQ-5D) and the EQ-VAS [34] will be used to measure the participant's quality of life, covering the domains of mobility, self-care, usual activities, pain/discomfort, and anxiety/depression, and overall health state (EQ-VAS). The EQ-5 D is a standardised instrument for measuring health related quality of life and providing a single index of utility, necessary for the calculation of a cost utility ratio in an economic analysis. It has been used for a range of conditions and changes in the EQ-5 D are significantly correlated with changes in condition-specific measures over three months (*p*= 0.01) [35].

The Functional Independence Measure (FIM) [36] will be used to assess the amount of assistance required to complete activities including feeding, dressing, transfers, walking, stairs, and cognitive function. The FIM has demonstrated strong psychometric qualities in rehabilitation settings with high levels of reliability (ICC = .96) [37] and evidence for responsiveness and validity as a global disability measure for patients receiving rehabilitation [38].

Follow-up measures of the FIM and EuroQol at 6 and 12 months will be collected by telephone by assessors blinded to group allocation. There is evidence that telephone administration is a valid method of assessing functional status in older patients after rehabilitation [39].

Health utilisation and cost data will be collected from the rehabilitation facilities (inpatient care), outpatient services, and via a patient health service utilisation questionnaire administered at 6 months and 12 months post intervention. The questionnaire will include questions on health service utilisation including allied health and medical services, pharmaceutical use, and hospital admissions. In addition, Medicare Australia claims records will be retrieved with patient permission for 12 months post discharge to determine health service use post discharge including allied health, medical services, pharmaceutical use and hospital admissions. The amount of physiotherapy and occupational therapy intervention (number of treatment sessions, discharge planning, equipment hire or purchase, team meetings, staff discussions and family meetings) received by each group will be recorded via each hospital's allied health access database program, including the additional Saturday interventions received by the intervention group and any missed sessions as a result of medical instability, patient refusal and a patient not being ready to attend treatment on time.

The use of these tools will enable us to complete a cost utility analysis examining the cost per quality adjusted life-year saved and cost per 10% change in functional independence. We will assess health related quality of life and functional status at both 6 months and 12 months to try and minimise loss-to-follow-up as an intention-to-treat analysis will be undertaken.

### Secondary outcome measures

Secondary outcomes measures include the 10 metre walk test [40], the timed up and go test [41], and the Personal Care Participation Assessment and Resource Tool (PC-PART) [42]. The modified motor assessment scale [43] will be completed on patients with a neurological diagnosis. All secondary outcome measures are designed to evaluate clinical outcomes relevant to the functional goals of therapy, and will be measured on admission and at discharge.

Discharge destination will be recorded as home, high level residential care, low level residential care, and acute hospital transfer. This will be recorded as "worse" when the participant was discharged to a destination where more assistance would be provided, for example a high level residential care facility, or "same" when a participant was discharged to the same place of accommodation prior to the hospital admission. This outcome measure is included to measure any increase in burden of care to the community.

Demographic data on participant age, gender and co-morbidities will be documented from each participant's medical chart. Co-morbidities will be recorded using the Charlson co-morbidity index [44].

Adverse events, including falls, nosocomial infections and mortality will be recorded on an incident report form through an audit of participants at discharge and the rehabilitation facilities' incident reporting database. Follow-up physiotherapy and occupational therapy will be recorded at discharge as outpatient, community rehabilitation (including centre-based and home services), or no follow up.

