## Background

Reducing patient length of stay is a high priority for health service providers and is considered to be an indicator of efficiency [1,2]. The implications of a reduction in length of stay are potentially significant for the individual, the health service and for the community. A reduction in length of stay means the individual can return to their community sooner, that individuals may not have to wait so long for a bed, that the health service can treat more patients, and that there are cost savings for the community. However, from the perspective of the health system, if reducing length of stay is achieved at the expense of quality of care, this will reduce efficiency and could increase pressures and costs to other health services. Despite this concern, there is some evidence, at least in acute hospitals, that reducing length of stay has not been achieved at the expense of quality of care [3,4].

The allied health team, including physiotherapists and occupational therapists, play a key role in the effective management of patients receiving rehabilitation for neurological and musculoskeletal conditions [5-10]. Physiotherapy and occupational therapy aim to increase the independence of patients receiving rehabilitation by improving mobility and self-care skills. Developing independent mobility and self care skills are important physical factors in predicting the need for long-term placement [11] and are associated with better quality of life [12]. Therefore, attaining mobility and self-care skills are important in determining whether patients receiving rehabilitation can successfully return home to participate in their usual societal activities and improve their quality of life.

There has been an increased focus on the importance of intensity and activity in rehabilitation. During early rehabilitation, patients receive relatively little therapy and have low levels of physical activity [13]. Reports that increasing the intensity of rehabilitation could be associated with improved outcomes [14] have led to calls for rehabilitation to be more active and intensive [15,16]. Previous studies have indicated that the intensity of physiotherapy and occupational therapy provision may affect patient outcomes leading to reduced mortality following stroke [17], and improved functional status following brain injury [18], stroke [17,19], and femoral fracture [20].

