One way to increase the intensity of rehabilitation is to provide additional allied health services. Typically, allied health rehabilitation services are provided Monday to Friday. Weekend services have not been provided, have been provided on a much reduced scale, or have only been provided to patients at risk of an acute event such as due to a chest infection [21-24]. A recent systematic review provided preliminary evidence that additional allied health services can reduce length of stay in hospital for patients receiving rehabilitation [25]. There was evidence that additional weekend physiotherapy significantly decreased length of stay for patients who had undergone elective hip and knee joint arthroplasty [26] and patients with non-surgical stroke [27]. However, trial quality in the systematic review was only fair, with only three of nine included studies using a randomised control design.

Our pilot study examined the effect of additional Saturday physiotherapy for rehabilitation inpatients [28]. Two hundred and sixty two participants were included in this randomised controlled trial. The mean patient length of stay was 24.4 days (SD 15.9) for patients who received a Monday to Friday physiotherapy service and 21.2 days (SD 14.0) for patients who received a Monday to Saturday service. The 3.2 day difference demonstrated a trend in favour of the intervention group (95% CI -0.5 to 6.9 days, *p*= 0.09). Assuming a maintained effect size of 0.21 and power of 0.80, then 356 participants would have been required in each group to reach statistical significance.

Patient quality of care was not adversely affected by a shortened hospital stay [28]. There were no differences in function, quality of life and discharge outcomes between the Monday to Friday service and the Monday to Saturday service. Quality of life was not significantly different between the groups at discharge or at follow-up. There was no significant difference between groups in the change from admission to discharge for the secondary outcome measures of functional independence measure, timed 10 metre walk test, timed up and go, and the modified motor assessment scale. There were also no significant differences in discharge destination, adverse events or follow-up therapy between the groups.

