In a healthcare system with fixed capacity even a small saving in length of stay can be important. The Australasian College for Emergency Medicine recently reported that if a hospital with 20,000 admissions each year saved half a bed day per patient by improving discharges, about 2000 extra patients a year could be admitted [29]. Data from our pilot study suggests that if the average length of stay from each rehabilitation episode was reduced by 3.2 days, there would be an additional 68 patients admitted to a typical 30-bed rehabilitation facility each year [28]. These results have the potential to increase patient flow from the acute to the subacute setting providing increased capacity in the acute care setting. A rigorous health economic evaluation in a larger trial is required to confirm the cost effectiveness of providing additional allied health services for rehabilitation.

In summary, to evaluate the potential benefits of the provision of additional Saturday allied health services to rehabilitation inpatients, we will conduct a fully powered randomized controlled clinical trial that will: complete an economic analysis of additional allied health services compared with the traditional Monday to Friday usual care service from a healthcare system perspective; and incorporate occupational therapy rehabilitation services in addition to physiotherapy.

The primary aim of this trial is to determine if the provision of additional Saturday allied health services will reduce the costs of care by reducing patient rehabilitation length of stay without affecting health related quality of life and functional outcomes compared to those receiving usual care. The secondary aims are to examine if the provision of additional Saturday allied health services has any effect on therapeutic functional goals at discharge; or the use of community-based health services post discharge from the sub-acute hospital setting, compared to those receiving usual care. For the purpose of this clinical trial the term "allied health" will specifically refer to physiotherapy and occupational therapy services.

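### Adverse events are collected only up to discharge, which the intervention is meant to bring forward, so later falls, deaths and infections managed without admission are not recorded as safety outcomes

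*Protocol article*

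**What the plan says.** Protocol article, Secondary outcome measures: "Adverse events, including falls, nosocomial infections and mortality will be recorded on an incident report form through an audit of participants at discharge". The second source is "the rehabilitation facilities' incident reporting database". Both sources describe the stay in the rehabilitation unit. The functional secondary measures in the same section "will be measured on admission and at discharge". No collection of adverse events after discharge is described, and no fixed observation period is set.

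The Background gives the primary aim, which is to "reduce the costs of care by reducing patient rehabilitation length of stay without affecting health related quality of life and functional outcomes". It also names the risk to be ruled out, namely the loss to the health system "if reducing length of stay is achieved at the expense of quality of care".

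Other data do continue after discharge. Under Primary outcomes measures: "Follow-up measures of the FIM and EuroQol at 6 and 12 months will be collected by telephone by assessors blinded to group allocation". The same section plans a service-use questionnaire at 6 and 12 months that covers hospital admissions, and 12 months of Medicare claims. Discharge destination is recorded as a marker of burden on the community. The sections on statistical analysis name no method for adverse events.

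**The concern.** The end of the safety record is set by discharge, and discharge is what the intervention is meant to change. Two consequences follow.

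- The harm most specific to leaving earlier (a fall at home, an infection that appears later, a death) occurs after adverse event recording has closed. A later analysis plan cannot recover events that were never collected.
- Participants in the arm with the shorter stay are watched for fewer days. A crude comparison of in-hospital events would then favour that arm even if daily risk were the same.

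At stake is how firmly the trial can say that a shorter stay was safe. The pilot summary in the Background lists the absence of a difference in adverse events among its evidence that care was not harmed by a shorter stay, so the new trial's adverse event data may well be used in the same way.

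**Working it through.** **1. The plan's own figure.** Sample size estimation gives 356 per group for effect size 0.21 and power 0.80. With two-sided alpha 0.05 (assumed; the article does not state it), n = 2(1.95996 + 0.84162)² / 0.21² = 2 × 7.849 / 0.0441 = 355.96, so 356. The figure reproduces and is used below. Nothing in this point changes it.

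**2. What would be seen after discharge.**

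| Event after discharge | Where the article would capture it |
|---|---|
| Fall without admission | Not identified as a fall; any medical visit appears only as service use |
| Infection managed without admission | Not identified as an infection; treatment appears only as service or drug use |
| Fall or infection leading to admission | Questionnaire at 6 and 12 months, and claims, as utilisation and cost |
| Lasting decline | FIM and EuroQol at 6 and 12 months |
| Death | No collection described |

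**3. Exposure in hospital.** Control input from the pilot (Background): "The mean patient length of stay was 24.4 days (SD 15.9) for patients who received a Monday to Friday physiotherapy service". In the same paragraph, the six-day arm of the pilot averaged 21.2 days, with an SD of 14.0.

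- Ratio of observed days: 21.2 / 24.4 = 0.869, or 13.1% less time in the intervention arm.
- Patient-days at 356 per arm: 356 × 24.4 = 8,686 and 356 × 21.2 = 7,547, a gap of 1,139.
- Daily rate increase that would still give equal counts: 24.4 / 21.2 = 1.15, or 15%.
- Range from the pilot interval (-0.5 to 6.9 days), holding the control stay at 24.4: 17.5 / 24.4 = 0.72 to 24.9 / 24.4 = 1.02.

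**4. Proportions with at least one event, equal daily hazard h.** Risk = 1 - exp(-h × stay), with h set by the control risk over 24.4 days. The article gives no event risk, so the control risks are assumptions.

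| Control risk (assumed) | Intervention risk | Risk ratio, fixed stay | Risk ratio, gamma-distributed stay (pilot SDs) | Chance of a significant result favouring intervention |
|---|---|---|---|---|
| 5% | 4.36% | 0.872 | 0.873 | 6.0% |
| 10% | 8.75% | 0.875 | 0.877 | 8.3% |
| 20% | 17.62% | 0.881 | 0.885 | 12.5% |
| 30% | 26.65% | 0.888 | 0.894 | 16.7% |

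The last column uses 356 per arm and two-sided alpha 0.05; with equal exposure it would be 2.5%. The reduction is 13% in counts, about 12 to 13% in proportions for control risks up to 20%, and about 11% at 30%.

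**5. Share of time covered.** With follow-up to 12 months after discharge, adverse event recording covers 24.4 / (24.4 + 365) = 6.3% of a control participant's time under study and 21.2 / (21.2 + 365) = 5.5% of an intervention participant's.

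**The case against.** The strongest reply is that the trial does look beyond discharge. Hospital admissions, service use, function and quality of life are followed to 12 months, readmission to the participating facilities is costed, and discharge destination includes acute transfer. A reader might infer that harm from early discharge goes unrecorded. The article does not support that: harm serious enough to cause admission or lasting decline would show. This stands, and it narrows the point to falls and infections managed without admission, and to deaths. One qualification applies. Statistical analysis fills missing health outcome data by carrying the last value forward and makes no exception for death. As written, a participant who died after discharge would keep earlier FIM and EuroQol values, so those outcomes cannot be relied on to reveal late deaths.

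A reader might also infer that the safety comparison is biased towards the intervention by design. That needs a crude per-patient analysis, which the article does not specify. The method of analysis may be left to the analysis plan, and rates per patient-day would remove the exposure effect for in-hospital events. This also stands, so the 12 to 13% is conditional.

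Third, fewer hospital-acquired infections after a shorter stay can be a real benefit. Likewise, fewer ward falls are only an artefact if falls continue at home, and the document has no figure for that. This stands.

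Finally, the stated aim rests on quality of life and function, not on adverse event counts. That is correct and limits the weight of the point. It does not close the gap in collection.

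**Conclusion.** The point holds in a limited form. Adverse event collection ends at a time that depends on treatment. Falls, infections managed without admission, and deaths after discharge are not recorded as safety outcomes. The gap lies in data collection, so it cannot be repaired at the analysis stage.

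The in-hospital distortion is modest: about 12 to 13% fewer events in the intervention arm with no true difference in daily risk. It assumes that the pilot difference of 3.2 days is maintained (it was not statistically significant), a constant and equal daily hazard, and a crude comparison. The article supports neither the conclusion that early-discharge harm is wholly invisible nor that the safety result is biased whatever the analysis. The primary analysis and the sample size are unaffected. This is an inexpensive improvement that would strengthen any statement that earlier discharge is safe.

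**What to change.** In Secondary outcome measures:

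1. Add falls, infections and vital status, each with the date of the event, to the 6 and 12 month contacts already planned.
2. Compare falls and deaths between arms over one common period counted from randomisation. The Abstract times the contacts from discharge, so event dates are essential. Discharge follows randomisation, so the 12 month contact always falls later than 12 months after randomisation, and a 12 month period is covered for everyone reached.
3. Keep nosocomial infections as an in-hospital outcome, separate from infections reported after discharge.
4. Show in-hospital falls and infections per 1,000 patient-days alongside the per-patient figures. The rate shows daily risk; the per-patient figure keeps any real benefit of a shorter stay visible.

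The cost is a few questions on scheduled calls and a denominator from length of stay already recorded. The downside is that falls and infections after discharge would be self-reported and less complete than ward reports. The loss may not be equal between arms, because the arm with the longer stay spends more of the common period under ward reporting. The report should say so.

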## Data analysis

### Sample size estimation

Sample size estimation is based on rehabilitation length of stay data [28]. For length of stay, with a maintained effect size of .21 and power of 0.80 a sample size of 356 participants in each group is required (total of 712 participants).

### Statistical analysis

Between group differences of the primary outcomes (length of stay, EuroQol, and FIM) will be analysed with analysis of covariance of discharge scores with the baselines score as covariate [45]. Intention to treat analysis will be used with any missing health outcome data imputed using the last value carry forward method [46].

A rigorous economic evaluation will be carried out alongside the randomised clinical trial. Cost effectiveness of the intervention will be determined as the incremental cost of additional Saturday allied health inpatient rehabilitation services compared to usual inpatient rehabilitation per quality adjusted life year saved. The primary measure of incremental effect for the economic evaluation will include the difference in health related quality of life between the control and treatment groups using the EuroQol. A secondary incremental cost effectiveness ratio will be determined using the cost per change in functional status using the FIM.

Patient level costing and utilisation data for inpatient rehabilitation services from the hospital's costing and admission and discharge system will be used to estimate the costs of inpatient care. Following discharge, the patient health service utilisation questionnaire will be administered at 6 and 12 months to determine the health care services used post discharge. Costs will be attributed to these services based on published costing data from the National Hospital Cost Data Collection, Medicare Australia, and the Pharmaceutical Benefits Scheme. Where a patient is re-admitted to one of the participating rehabilitation facilities within the 12-month period inpatient costing data will be used. Medicare Australia data will be used to obtain private health service utilisation. The costs of implementing the intervention (Monday to Saturday rehabilitation) and the control programs (Monday to Friday rehabilitation) will be determined from the rehabilitation facility. This will include therapist time, equipment, consumables and administrative overheads. The incremental cost estimate will be determined as the difference in cost of implementing the Saturday allied health rehabilitation service plus the difference in health service costs (including out-of-pocket private expenditure) used in the 12 months post discharge between the control and intervention groups. A secondary incremental cost estimated will be calculated as the change in resource use resulting from the additional Saturday allied health rehabilitation service compared to usual Monday to Friday rehabilitation at the point of discharge from the inpatient rehabilitation facility. Any missing health service utilisation or cost data, where service use was recorded but a quantity not specified, will be imputed using within group mean cost [47].

The primary health economic analysis is a cost utility analysis from a health care system perspective, with outcomes based on health related quality of life (using EuroQol), and cost effectiveness using an intermediate clinical outcome (based on the FIM). We will be undertaking an intention to treat analysis where the cost utility ratio will be calculated as the change in total program and health service cost per change in quality adjusted life year saved in the intervention and control groups at 6 and 12 months. Additional cost effectiveness ratios will be calculated as the total program cost per 10% change in functional independence (at discharge), and the total program and health service cost per 10% change in functional status between the control and intervention groups over a 12 month period. One way sensitivity analysis will be undertaken to investigate the robustness of the cost effectiveness ratio to a range of cost and effect estimates, including alternative delivery arrangements, wage rates and program length on the cost side, and health related quality of life and FIM on the effect side.

Between group differences of secondary outcomes measured on continuous or ordinal scales will be analysed with analysis of covariance of discharge scores with the baselines score as covariate [45]. Between-group differences in discharge destination (home versus other) will be analysed with relative risk ratios.

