**Methods/Design:**

A randomised controlled trial will evaluate the effect of providing additional physiotherapy and occupational therapy for rehabilitation. Seven hundred and twelve patients receiving inpatient rehabilitation at two metropolitan sites will be randomly allocated to the intervention group or control group. The control group will receive usual care physiotherapy and occupational therapy from Monday to Friday while the intervention group will receive the same amount of rehabilitation as the control group Monday to Friday plus a full physiotherapy and occupational therapy service on Saturday. The primary outcomes will be patient length of stay, quality of life (EuroQol questionnaire), the Functional Independence Measure (FIM), and health utilization and cost data. Secondary outcomes will assess clinical outcomes relevant to the goals of therapy: the 10 metre walk test, the timed up and go test, the Personal Care Participation Assessment and Resource Tool (PC PART), and the modified motor assessment scale. Blinded assessors will assess outcomes at admission and discharge, and follow up data on quality of life, function and health care costs will be collected at 6 and 12 months after discharge. Between group differences will be analysed with analysis of covariance using baseline measures as the covariate. A health economic analysis will be carried out alongside the randomised controlled trial.

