### Randomisation

Participants will be randomised to the additional allied health services (intervention) group or the control group with a concealed method, using permuted blocks of 4, 6 and 8, stratified for case-mix status (neurological and other/orthopaedic) and site (two sites). Stratification will include site in order to facilitate the staffing of the Saturday service. The block allocation sequence will be generated by http://www.randomization.com and assignments sealed in sequentially numbered opaque envelopes. Only after the participant has enrolled in the trial and completed written informed consent and baseline testing will assignment be made by the project officer by opening the next envelope in the sequence. A member of the research team who is not involved in participant recruitment, assessment or treatment will be responsible for preparing the envelopes.

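### Length of stay, the outcome that sizes the trial, is assigned an ANCOVA on a baseline score it does not have; it needs its own stated model

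*Protocol article*

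**What the plan says.** The Statistical analysis section of the protocol article puts the three primary outcomes under one rule: "length of stay, EuroQol, and FIM) will be analysed with analysis of covariance of discharge scores with the baselines score as covariate". It repeats the baseline-score rule for secondary outcomes on continuous or ordinal scales. The Abstract (Methods/Design) is looser: "Between group differences will be analysed with analysis of covariance using baseline measures as the covariate".

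Under Primary outcomes measures, the outcome is defined thus: "Patient length of stay will be measured as the number of overnight stays in the rehabilitation unit, from the day of admission until the day". The count ends when the patient leaves the unit.

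Under Sample size estimation: "Sample size estimation is based on rehabilitation length of stay data". The calculation follows: "with a maintained effect size of .21 and power of 0.80 a sample size of 356 participants in each group is required (total of 712".

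Under Randomisation, allocation is "stratified for case-mix status (neurological and other/orthopaedic) and site (two sites". That section also places baseline testing before allocation, and the Abstract says outcomes are assessed at admission and discharge.

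**The concern.** EuroQol and FIM are measured at admission and again at discharge, so baseline-score ANCOVA suits them. Length of stay is different. It builds up only after admission and is complete only at discharge, so the covariate named for it does not exist. The rule is therefore inapplicable to the outcome that justifies 712 patients, and whoever runs the analysis must put something in its place.

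Two things are at stake. First, the published text does not say which length-of-stay comparison is the planned one. Second, the fallback of no adjustment leaves unused the admission FIM and the stratification factors, which may predict how long a patient stays.

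**Working it through.** **Can the model be fitted?** ANCOVA here is: discharge value = intercept + treatment effect + slope × baseline value + error. For length of stay, the value at admission is zero for every patient. A covariate that is the same for everyone cannot be separated from the intercept, so the slope cannot be estimated. What remains is intercept + treatment effect, which is the unadjusted difference in mean nights.

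**Does any other section supply a covariate?** The Abstract's wording could cover some other admission measure but names none. The rest of the Statistical analysis section does not return to the length-of-stay model.

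**Reproducing the sample size.** Inputs from Sample size estimation: effect size d = 0.21, power 0.80. The significance level is not stated; two-sided 0.05 is assumed because it returns the stated figure (one-sided 0.05 gives 281 per group).

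n per group = 2 × (1.96 + 0.8416)² / 0.21² = 355.96, that is 356, or 712 in total. This matches. An exact t-test calculation gives 357 per group, or 79.9% power at 356.

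The effect size agrees with the pilot in the Background. For the control arm: "The mean patient length of stay was 24.4 days (SD 15.9) for patients who received a Monday to Friday physiotherapy service". For the intervention arm, the Background gives a mean of "21.2 days (SD 14.0) for patients who received a Monday to Saturday service". Pooled SD = √((15.9² + 14.0²)/2) = 14.98 days, and 3.2/14.98 = 0.214.

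The planned 356 is thus the size for an unadjusted comparison of two means. It takes no credit for a covariate.

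**What adjustment could add.** If the baseline covariates have multiple correlation R with length of stay, the residual SD is multiplied by √(1 − R²). Power at 356 per group is then Φ(0.21/√(1 − R²) × √(356/2) − 1.96). For R = 0.4: 0.21/0.9165 × 13.342 = 3.057; 3.057 − 1.96 = 1.097; Φ(1.097) = 0.864. The 95% CI half-width is 1.96 × 14.98 × √(2/356) × √(1 − R²). The protocol gives no value for R, so each row below is an assumption.

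| R (assumed) | Power at 356 per group | 95% CI half-width, days | n per group for 80% power |
|---|---|---|---|
| 0 | 80.0% | 2.20 | 356 |
| 0.2 | 81.6% | 2.16 | 342 |
| 0.3 | 83.6% | 2.10 | 324 |
| 0.4 | 86.4% | 2.02 | 300 |
| 0.5 | 89.9% | 1.91 | 267 |

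**The case against.** The best defence is that little harm follows. With no usable baseline value, the rule falls back to a comparison of means. That comparison is valid under randomisation, is the one the trial was sized for, and is how the Background reports the pilot. The Abstract's broader wording also suggests that one sentence was condensed across three outcomes. All of this stands and limits the severity. It does not remove the error: the section names length of stay explicitly and gives it a covariate that it lacks.

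Three stronger readings are tempting, and the document supports none of them.

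- *The trial loses power.* It does not. Power stays at the planned 80% without adjustment; precision is lost only relative to an adjusted analysis that was never planned.
- *Covariates will be chosen after unblinding.* Nothing in the article plans this, and a statistical analysis plan that is not shown could fix the list beforehand.
- *Leaving the strata out of the model is itself an error.* A condensed article may leave that to a fuller plan, and the stated ANCOVA runs as written for EuroQol, FIM and the secondary outcomes. Standard errors would be too large only if the strata predict outcome. The article gives no data on that, and its stated reason for including site is the staffing of the Saturday service.

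**Conclusion.** The point holds as a specification error that should be fixed. The model stated for length of stay cannot be fitted as written, and nothing else in the article repairs it. This conclusion follows from the outcome's definition and needs no assumption.

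The consequence is modest. The default comparison is valid and keeps the planned power of about 80%. The possible gain from adjustment runs from nothing at R = 0, through 1.6 percentage points of power at R = 0.2 and 6.4 at R = 0.4, to 9.9 at R = 0.5. Those figures rest on assumed correlations, d = 0.21 and two-sided 0.05. They measure an available improvement, not a deficit against the plan.

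**What to change.** Give length of stay its own sentence in the Statistical analysis section: a linear model with treatment, site, case-mix stratum and admission FIM total, reporting the adjusted mean difference in days with a 95% CI. Make the covariate list fixed, with no optional terms, since optional covariates would reopen the choice that the sentence is meant to close.

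Keep baseline-score ANCOVA for EuroQol, FIM and the continuous or ordinal secondary outcomes, and add site and case-mix because randomisation was stratified on them. Bring the Abstract's wording into line, and settle the text before unblinding.

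The cost is one or two sentences. Site and case-mix are known at randomisation and FIM is assessed at admission, so no new data are needed and the sample size need not change.
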